### 3. Objectives

Overall, our aim is to investigate long-term kidney outcomes after recorded SARS-CoV-2 infection in the general population.

Our specific objectives are:

1. To describe the relative and absolute rates of ESRD (primary outcome) after recorded SARS-CoV-2 infection compared to both contemporary and historical groups, stratified by:
  - a. Hospitalisation for COVID-19
  - b. Critical care admission for COVID-19
  - c. Mechanical ventilation for COVID-19
  - d. Acute KRT associated with COVID-19
  - e. AKI associated with COVID-19
2. To describe the relative and absolute rates of a 50% reduction in eGFR, incident AKI, and death (secondary outcomes), after recorded SARS-CoV-2 infection compared to both contemporary and historical groups, stratified by:
  - a. Hospitalisation for COVID-19
  - b. Critical care admission for COVID-19
  - c. Mechanical ventilation for COVID-19
  - d. Acute KRT associated with COVID-19
  - e. AKI associated with COVID-19
3. To describe the relative and absolute rates of these outcomes after hospitalisation for COVID-19 compared to a historical hospitalised group, stratified by:
  - a. Critical care admission for COVID-19
  - b. Mechanical ventilation for COVID-19

- c. Acute KRT associated with COVID-19
  - d. AKI associated with COVID-19
- 4. To describe the relative and absolute rates of outcomes after recorded SARS-CoV-2 infection compared to both contemporary and historical groups stratified by:
  - a. Baseline eGFR
  - b. Diabetes
  - c. Age
  - d. Sex
  - e. Ethnicity
  - f. Socioeconomic deprivation
- 5. To describe the relative and absolute rates of outcomes after recorded SARS-CoV-2 infection compared to both contemporary and historical groups additionally stratified by:
  - a. Calendar time
  - b. Vaccination status

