#### **4.4.4 Follow-up start**

By using index dates 28 days after first recording of SARS-CoV-2 infection (i.e., date of testing in SGSS, date of primary care coding, or date of admission on SUS), we will be able to look back and further stratify the exposure by measures of SARS-CoV-2 severity (i.e. community, hospitalisation, critical care admission etc.).

For analyses comparing people after SARS-CoV-2 infection to a historical comparator group from 2018-2019, the matched historical comparators will be followed-up from exactly two years before the index date.

For analyses comparing people hospitalised for COVID-19 with an unmatched historical group of individuals hospitalised for pneumonia from 2018-2019, we will follow all eligible individuals from 28 days after their admission date for pneumonia.

For analyses comparing people after SARS-CoV-2 infection to a matched contemporary comparator group, we will follow all eligible individuals from the index date.

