#### **4.4.5 Follow-up end**

In all analyses we will follow individuals until the earliest of: record of specific kidney outcome under investigation, ESRD, death, no longer registered with GP practice, or study end. Individuals from the matched contemporary comparator group will also be censored at the date of first recorded SARS-CoV-2 infection and will transfer to the exposed group if they survive 28 days after this date.

For analyses using matched historical 2018-2019 comparators, the study end for people with COVID-19 will be the last available date for data at the time of extraction, and for

their matched comparators it will be January 31 2020 at the latest. Our choice of end of follow-up for people with COVID-19 is to be consistent with the available follow-up time for people in the historical comparator group, as we will no longer be able to follow people in the historical comparator group after February 2020 (as we will no longer be sure that those in our comparator group did not have COVID-19 after the start of the initial UK COVID-19 outbreak in February 2020). By allowing the same duration of potentially available follow up for people with and without COVID we will be able to ensure our results are not biased by allowing additional follow up for people with COVID-19 (and consequently allowing more time for them to develop the outcomes under investigation) compared to those without. By allowing the same duration of potentially available follow up for people with and without SARS-CoV-2 infection, we will be able to ensure our results are not biased by allowing additional follow up for people pre-pandemic.

For analyses with the contemporary comparator group, the study end will be the latest available date of fully linked data available on the day the initial cohort is extracted.

[figure not shown]

[figure not shown]

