## 4.5 Study measures

### 4.5.1 Exposure

We will identify recorded SARS-CoV-2 infection using data from SGSS, primary care records and SUS. We will include all codes indicative of SARS-CoV-2 infection. SGSS contains the date of an individual's earliest positive SARS-CoV-2 test results from Pillar 1

(NHS and Public Health England laboratories) and Pillar 2 (commercial partners) between 1 February 2020 to the most recent available time point (i.e. the COVID-19 pandemic era).

Individuals meet criteria for inclusion in the COVID-19 exposed group if they:

- Tested positive for SARS-CoV-2 infection in SGSS
- Had a primary care code indicative of SARS-CoV-2 infection
- Discharged from hospital with an International classification of Diseases Version 10 (ICD-10) code in SUS indicative of COVID-19

The index date for those exposed to COVID-19 will be from 28 days after first recording of SARS-CoV-2 infection (i.e., after the earliest date of the record of a positive test in SGSS, primary care coding, or admission in SUS).

Looking at all identified SARS-CoV-2 infections will allow us to investigate how many adverse kidney outcomes can be prevented by preventing SARS-CoV-2 infection altogether through comparisons with people from the general population without known infection. We will also be able to investigate whether outcomes vary based on infection severity (hospitalisation, critical illness, mechanical ventilation and AKI [including requiring RRT]) as well as calendar time and vaccination status through further stratification based on morbidity coding (ICD-10 codes) from SUS. We will categorise people as i) unvaccinated if they had not received any vaccine dose at least 7 days before first recording of SARS-CoV-2 infection, ii) single dose vaccinated if they had received one vaccine dose at least 7 days before first recording of SARS-CoV-2 infection, iii) double vaccinated if they had received two vaccine doses at least 7 days before first recording of SARS-CoV-2 infection, and iv) more than double vaccinated if they had received more than two vaccine doses (including booster doses) at least 7 days before first recording of SARS-CoV-2 infection.

Hospitalised COVID-19 cases will be further investigated through a separate comparison with a historical group. Additional levels of exposure for those hospitalised will include critical care admission, mechanical ventilation, acute KRT and AKI, determined from ICD-10 and procedural codes in SUS.

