### **4.6.3 Secondary analyses**

1. We will use Cox regression models to estimate cause-specific hazard ratios and 95% confidence intervals for the secondary outcomes i) 50% reduction in eGFR, ii) AKI and iii) death for individuals after SARS-CoV-2 (stratified as above) compared to individuals in the i) historical and ii) contemporary comparator groups.
2. We will undertake further Cox regression models for both primary and secondary outcomes with SARS-CoV-2 infection stratified by calendar time (i.e. February –

June 2020, July – September 2020, October – November 2020, December 2020 – February 2021, and March – January 2022) and vaccination status.

3. We will fit interaction terms to obtain cause-specific hazard ratio estimates for both primary and secondary outcomes stratified by age group, ethnicity, socioeconomic deprivation, diabetes and baseline eGFR.
4. For people who survive 28 days after hospitalisation for COVID-19, we will undertake an unmatched cohort analysis comparing kidney outcomes with a historical population followed-up from 1 February 2018 restricted to those who survived 28 days after a hospital admission for pneumonia (with or without influenza). This analysis will be stratified by critical care admission, mechanical ventilation, acute KRT and AKI, with additional adjustment for calendar month. The reason for this analysis is to investigate whether COVID-19 is responsible for long-term kidney outcomes to a greater or lesser extent than hospitalisation for other respiratory tract infections.

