| 4.3 Study designs                  | We will compare people after SARS-CoV-2 infection to both historical and contemporary cohorts in order to address epidemiological challenges to be able to triangulate meaningful conclusions.                                                                                                                                                                                                                                                                             | The comparison with the historical cohort was designated as a sensitivity analysis.                                                                                                                        | 
We had expected the analysis with contemporary comparators may not be robust due to non-ascertainment of asymptomatic/mild COVID-19 infection. However, because of the absence of effect in those with non-hospitalised COVID-19, this did not prove to be an important bias.
 
For clarity and avoidance of repetition, we assigned our historical cohort analysis as a sensitivity analysis in our final manuscript.
 |
| 4.4.2 Historical comparator groups | 
[We will match historical comparators] 2 years before the first recording of SARS-CoV-2 infection in the exposed case....
 
In our secondary analysis, we will compare individuals who remain alive 28 days after admission to hospital with COVID-19 with those who remained alive 28 days after admission to hospital for pneumonia (including influenza) from 1 February 2018 up to two years before the end of follow-up for the exposed group (unmatched)
 | 
We matched historical comparators three years before first recording of COVID-19 infection.
 
For secondary analysis, we followed-up patients hospitalised for pneumonia from 1 February 2017.
 | This allowed us to follow-up COVID-19 cases up to 31 January 2023 and historical comparators up to 31 January 2020 (i.e., before the start of COVID-19 epidemic in the UK).                                                                                                                                                                                                                                                        |

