| 4.6.1 Main analyses | 
Due to the competing risk of death, we will use Fine and Gray regression models (using calendar time as the underlying timescale) to estimate subdistribution hazard ratios...
 
We will run sequential regression models:
 
 
1. Minimally adjusted for age (using spline functions) and sex,
 
2. Additionally adjusting for ethnicity, IMD, smoking and BMI,
 
3. Additionally adjusting for clinical comorbidities.
 
 | 
We used Cox models stratified by matched set to obtain hazard ratios, overall, and stratified by time period instead of Fine and Grey models.
 
We ran fully-adjusted models only.
 
We undertook complete case analysis without making assumptions about individuals with missing BMI or smoking status data.
 | 
Cox models quantify average cause-specific hazards over the course of follow-up, as well as more meaningful period-specific hazards. These are more informative for policymaking than subdistribution hazards.
 
We ran only fully-adjusted models to be able to present the most meaningful estimates only after adjustment for potential confounding variables.
                                                                                                                           |

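### Whole-follow-up hazard ratios for infection periods with unequal follow-up cannot be clearly compared if the hazard ratio changes with time since infection

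*Protocol*

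**What the plan says.** Objective 5 (protocol section 3) is "To describe the relative and absolute rates of outcomes after recorded SARS-CoV-2 infection compared to both contemporary and historical groups additionally stratified by" calendar time and vaccination status. Section 4.6.3 item 2 carries this out with Cox models for all outcomes by period of infection, from February to "June 2020, July – September 2020, October – November 2020, December 2020 – February 2021, and March – January 2022) and vaccination status". No year is printed for March in the last band.

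On the start of follow-up, section 4.5.1 says: "The index date for those exposed to COVID-19 will be from 28 days after first recording of SARS-CoV-2 infection". For matched contemporary comparators, section 4.4.4 says "we will follow all eligible individuals from the index date".

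On the end of follow-up, section 4.4.5 says that in the contemporary comparison "the study end will be the latest available date of fully linked data available on the day the initial cohort is extracted". In the historical comparison the exposed are followed to the last date with data, and for "their matched comparators it will be January 31 2020 at the latest". That section argues for equal follow-up between exposed and unexposed. It does not address equal follow-up between one infection period and another.

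The table of deviations at the end of the document (row 4.4.2) moves the historical shift to three years: "This allowed us to follow-up COVID-19 cases up to 31 January 2023 and historical comparators up to 31 January 2020". Row 4.6.1 explains the choice of model: "Cox models quantify average cause-specific hazards over the course of follow-up, as well as more meaningful period-specific hazards". Row 4.5.1 says that calendar time and vaccination status became interaction terms. Row 4.6.2 says that stratum-specific hazard ratios were obtained overall and by hospitalisation status.

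**The concern.** The strata are defined by date of infection and all close on one administrative date, so early periods accrue much more late follow-up than recent ones. A single Cox hazard ratio per stratum averages over whatever follow-up that stratum has. If the relative hazard is higher soon after infection, a stratum with short follow-up gives a higher average than one with long follow-up, even when the underlying effect is the same. Rates per stratum are open to the same problem when the absolute hazard changes with time since index.

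Two entries in the deviations table make a changing hazard ratio plausible. Row 4.5.1 counts acute renal replacement therapy recorded between infection and index as kidney failure on the first day of follow-up, which can concentrate events at time zero. Row 4.6.1 prefers hazard ratios by period of follow-up to the single average.

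At stake is how objective 5 is read. A difference between waves or vaccination levels could be taken as a change in the effect of COVID-19 when part of it comes from the length of follow-up. A real fall in risk could likewise be hidden.

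**Working it through.** The plan gives no figure for follow-up by period, so there is none to reproduce.

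**Inputs from the protocol.** Five infection bands (section 4.6.3), a 28-day lag to index (section 4.5.1), and a comparator cut-off of 31 January 2020 (section 4.4.5). With the two-year shift, that cut-off corresponds to 31 January 2022 for the exposed. The deviations table gives 31 January 2023.

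**Assumptions.** March in the last band is March 2021. Infections are spread evenly over each band. There is no censoring before the end date, and the baseline hazard is constant and low.

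**Step 1: potential follow-up.** Follow-up = end date − (infection date + 28 days), set to zero if negative.
- First band, 2022 end: 1 February 2020 gives 730 − 28 = 702 days and 30 June 2020 gives 580 − 28 = 552. The mean is (702 + 552)/2 = 627.
- Last band, 2022 end: 1 March 2021 gives 336 − 28 = 308 days, and infections from 3 January 2022 give none. Over 337 infection dates the mean is (308 × 309/2)/337 = 141.
- The 2023 end adds 365 days. The first band then has 917 to 1,067 days (mean 992) and the last has 337 to 673 (mean 505).

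The ratio of means, first to last, is 627/141 = 4.4 with the 2022 end and 992/505 = 2.0 with the 2023 end.

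**Step 2: average hazard ratio under one common curve.** Assume a hazard ratio of 3.0 to day 180 and 1.5 afterwards, the same in every band. The average is approximately (3.0 × early days + 1.5 × late days)/(all days).
- First band, 2022 end: (3.0 × 180 + 1.5 × 447)/627 = 1.93.
- Last band, 2022 end: mean early days are (180 × 181/2 + 128 × 180)/337 = 116.7, and late days are 141.2 − 116.7 = 24.5. The average is (3.0 × 116.7 + 1.5 × 24.5)/141.2 = 2.74.
- First band, 2023 end: (540 + 1.5 × 812)/992 = 1.77.
- Last band, 2023 end: (540 + 1.5 × 325)/505 = 2.03.

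| Infection band | Mean days, 2022 end | Average HR | Mean days, 2023 end | Average HR |
|---|---|---|---|---|
| Feb–Jun 2020 | 627 | 1.93 | 992 | 1.77 |
| Jul–Sep 2020 | 505.5 | 2.03 | 870.5 | 1.81 |
| Oct–Nov 2020 | 429 | 2.13 | 794 | 1.84 |
| Dec 2020–Feb 2021 | 353.5 | 2.26 | 718.5 | 1.88 |
| Mar 2021–Jan 2022 | 141 | 2.74 | 505 | 2.03 |

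The apparent rise from first to last band is 2.74/1.93 = 1.42 with the 2022 end and 2.03/1.77 = 1.15 with the 2023 end.

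**Step 3: sensitivity to the curve.**
- With 1.5 to day 180 and then 1.1, the 2022 end gives 1.21 and 1.43.
- The limiting Cox estimate with five comparators per case, for 3.0 to six months and then 1.2, runs from 1.72 to 2.70 (2022 end) or 1.53 to 1.85 (2023 end).
- The same calculation with 5 in month one, 2 to month six and then 1.2 runs from 1.58 to 2.43, or 1.44 to 1.67.
- A constant hazard ratio of 1.6 gives 1.60 in every band with either end date.

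**The case against.** Unequal follow-up alone does not bias a Cox hazard ratio; with a constant ratio the bands agree. Objective 5 is worded as description. Contemporary comparators share the exposed person's index date, so each within-band hazard ratio compares groups with the same potential follow-up. All of this stands, and it confines the point to comparisons between strata.

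The larger figure rests on an assumed curve and an inferred end date. This also stands: 31 January 2023 is the only calendar end date the document gives for the exposed, and there the spread is about 15%, not 42%.

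The deviations table reports a check of proportional hazards with Schoenfeld residuals and period-specific hazard ratios. This answers the concern in part for the main models. The table describes no split by time since infection within wave or vaccination level, though it does not say that none was made. An interaction term by itself still gives each wave an average over its whole follow-up.

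A reader might infer that infections from 3 January 2022 have no historical follow-up although January 2022 lies in the last band. That follows from the two-year shift, but the three-year shift in the deviations table resolves it.

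Fixed windows could also be called a modelling detail for a statistical analysis plan. The protocol does, however, set the strata, the start and the single end date that create the unequal follow-up.

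**Conclusion.** The point holds in a limited form. Potential follow-up differs between infection periods by a factor of about 4.4 (31 January 2022 end) or 2.0 (31 January 2023 end), and sections 4.4.5 and 4.6.3 set no common horizon. If the hazard ratio changes with time since infection, differences between periods may partly reflect that time and cannot be clearly read as a change in the effect of COVID-19. The illustrated spread is 1.93 to 2.74 or 1.77 to 2.03. It depends on the assumed curve, even spread of infections, a constant baseline hazard, no earlier censoring, and March being March 2021.

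A reader might go further and infer that differences between periods reflect follow-up instead of any change in effect, that later waves must show higher hazard ratios, or that objective 5 cannot be answered. The documents do not support this. They do not give the shape of the hazard ratio over time, and section 4.3 itself lists real changes in variants, treatment and testing that can coexist with the artefact.

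For vaccination level the same mechanism applies as far as levels differ in infection date. The protocol gives no such distribution, so no size is claimed.

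**What to change.** For the calendar-time and vaccination comparisons, report hazard ratios and rates per stratum within the same fixed windows since index, for example 0–180 days and later. Compare strata only within a window that all of them can reach. Keep full follow-up for the overall hazard ratio, and print the year for March in the last band.

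Choose the window to fit the actual end date. With 31 January 2023, every infection in the five bands has at least 337 days of potential follow-up, so a 180-day window excludes no one by infection date. With 31 January 2022, only infections up to 7 July 2021 reach 180 days, which is 129 of the last band's 337 dates (38%), so a shorter window would be needed. Capping follow-up at a horizon that some cannot reach leaves a residue: under the curve of 5, then 2, then 1.2, a six-month cap with the 2022 end gives 2.68 in the last band and 2.50 in the others.

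The change uses data already held and needs only further runs of planned models. The cost is fewer events per window and wider intervals, which matters most for ESRD, assumed at 0.02% in section 5.

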#### **4.6.4 Sensitivity analyses**

We aim to investigate the robustness of our primary and secondary analyses by exploring assumptions further using a range of sensitivity analyses, including:

1. Competing risk analysis

Due to the competing risk of death, we will undertake a competing risk analysis using Fine and Gray regression models to obtain subdistribution hazard ratios for ESRD.

2. Multiple imputation for ethnicity

In our main analyses, we will undertake a complete case analysis for ethnicity (i.e. only include individuals with recorded ethnicity data). In this sensitivity analysis, we will use multiple imputation for missing ethnicity data.

3. Complete case analysis for smoking and BMI

In our main analysis, we will assume that individuals without smoking status are non-smokers and that individuals without BMI have normal BMI. In separate sensitivity analyses, we will instead undertake complete case analyses (i.e. only including individuals with complete smoking and BMI data respectively).

4. ESRD definition

In case of possible residual misclassification of AKI as ESRD (where an individual has an eGFR  $<15\text{ml/min/1.73m}^2$ ), we will undertake a sensitivity analysis restricting only to people with new codes for dialysis or transplantation (i.e., incident KRT).

5. Incident eGFR  $<30\text{ml/min/1.73m}^2$

As healthcare services have been impacted heavily by the pandemic, there may not have been sufficient routine testing of patients to be able to detect a reduction in eGFR. As patients who are highest risk may be prioritised, we will also investigate for incident eGFR  $<30\text{ml/min/1.73m}^2$  in primary care or new codes for dialysis or kidney transplant in either primary care records, or ICD-10 or procedural codes from SUS.

6. eGFR equation

In our main analyses, we will calculate eGFR using the CKD-EPI equation from 2009 (without adjusting for ethnicity). This equation has recently been updated excluding adjustment for ethnicity. We will assess how many individuals change CKD stage from the original CKD-EPI equation after switching to the 2021 equation. If there are marked differences in the number of people with CKD and within each CKD stage, we will undertake a sensitivity analysis using the 2021 equation instead for eGFR.

